#### Termination of participation

2.3.6

Patient participation in the study may terminate for reasons such as withdrawal of informed consent, failure to commence treatment within the study, post enrolment screening failure, investigator's discretion (e.g., patient noncompliance), loss to FU, death, and other unspecified reasons. Detailed information explaining the reasons for termination will be recorded in a dropout form. For these patients, the collected data will be censored at the day of termination and may be used in the analysis.

#### Outcome measures

2.3.7

Outcome measures will be assessed according to the schedule in Tables 2, 3.

##### Adverse events

2.3.7.1

Safety will be assessed by the incidence of AEs that are related, probably related, or possibly related to the investigational device (i.e., adverse device effects [ADEs]) or the procedure. The events collected are described in the Supplementary Material.

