**Methods:**

Approximately 76 patients with clavicle fractures and primary surgical treatment with the 2.7 mm VA-LCP Clavicle Plate or 2.7 mm VA-LCP Clavicle Hook Plate will be enrolled prospectively over 15 months. Outcome measures include adverse events related/potentially related to the investigational device, clinical performance, functional outcomes (QuickDASH), PROs (PROMIS® upper extremity score, local pain, discomfort, and plate prominence), and radiographic outcomes. Data will be collected at baseline, 2w, 6w, 3m, 6m, 1y and 2y after surgery. The surgeons' experience with and perceived utility of the devices will be surveyed. Interim analysis will be performed when 30 patients per group have reached 6 months after surgery. Long-term outcomes will be evaluated using 2-year follow-up results. A Statistical Analysis Plan will be prepared before final analysis summarizing the descriptive statistics to be used.

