#### Unscheduled visits

2.3.5

Unscheduled visits outside of the defined timepoints may take place any time during the study in cases of medical emergency or if deemed appropriate for patient care. No data will be recorded in the eCRF except for any device or treatment related adverse events (AEs). Any images taken will be sent to the sponsor, and a drop out form will be completed if a patient drops out.

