AEs will be reported both at patient level and AE level. The risk estimates will be presented along with the 95% Clopper-Pearson confidence interval. When calculating the AE rates, the denominator will be the full analysis population, irrespective of dropouts during FU. Sensitivity analyses will be conducted excluding patients who dropped out of the study and had not experienced an AE. For patients treated with Clavicle Plates, the risk of experiencing any ADE within 24 months after surgery will be reported. For the calculation of the ADE rate, only ADEs with onset before or within the upper visit window of the 24 months visit will be included. For patients treated with Clavicle Hook Plates, the risk of experiencing any ADE between surgical treatment and 12 months after removal of the Clavicle Hook Plate will be reported. Separate sub analyses on the risk of experiencing an ADE between surgery and Clavicle Hook Plate removal and within 12 months after the Clavicle Hook Plate removal will be performed. Separate ADE rates for the two FU periods including only ADEs with onset within the upper boundary of the visit window of the corresponding FU period will be calculated. For incidences of complaints related to plate prominence or discomfort and to local pain, incidence rates will be calculated, and summary statistics presented, including the number and percentage of patients with complaints related to plate prominence or discomfort (defined as NRS ≥1) and local pain (defined as NRS ≥3). For the reoperation rate due to ADE, fracture union rate, rate of stable AC joint healing at one-year post-removal, the full analysis population will be used as the denominator. Descriptive analyses on the rate of implants removed and the reasons for implant removal will be conducted. Simple summary statistics (i.e., numbers and percentages) will be produced for each bone healing category. QuickDASH, will be measured repeatedly during the FU period and analyzed using mixed effects models for repeated measures (MMRM). PROs also measured repeatedly during the FU period will likewise be analyzed using MMRM. For the surgeons' evaluation, simple summary statistics including numbers and percentages will be produced for each category.

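### The safety outcome covers device- or procedure-related AEs, but every risk with a stated onset window counts device effects only

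*Protocol article*

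**What the plan says.** Section 2.3.7.1 (Adverse events) sets the safety outcome. It takes AEs judged related, probably related or possibly "related to the investigational device (i.e., adverse device effects [ADEs]) or the procedure", and refers to the Supplementary Material for the events collected. Section 2.3.5 (Unscheduled visits) has a similar scope for what is captured between scheduled visits: "No data will be recorded in the eCRF except for any device or treatment related adverse events (AEs").

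Section 2.4.2 (Statistical analysis) begins generally: "AEs will be reported both at patient level and AE level". It adds "The risk estimates will be presented along with the 95% Clopper-Pearson confidence interval", and takes the full analysis population as the denominator for AE rates regardless of dropout. It then gives the risks that have a time frame:

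- Clavicle Plates: "For patients treated with Clavicle Plates, the risk of experiencing any ADE within 24 months after surgery will be reported". Only ADEs with onset up to the upper limit of the 24-month visit window count.
- Hook Plates, whole period: "the risk of experiencing any ADE between surgical treatment and 12 months after removal of the Clavicle Hook Plate will be reported".
- Hook Plates, sub-periods: separate ADE rates from surgery to removal and for the 12 months after removal, again with an onset cut-off at the upper visit window.

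The Methods part of the abstract names only "adverse events related/potentially related to the investigational device" among its outcome measures.

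**The concern.** The analysis rule is narrower than the outcome it should estimate. Section 2.3.7.1 puts the abbreviation ADE in a parenthesis after the device and then adds the procedure as a second route into the safety outcome. An event judged related only to the procedure is part of safety as defined, but it is not an ADE. Section 2.4.2 uses the ADE label wherever it fixes a period and an onset rule.

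Safety is the first listed objective, and the study has no control group. A period-specific risk is the kind of figure a later comparative study would take from this one, and the Discussion names that use. Follow-up also differs by design. Clavicle Plates are followed for 24 months from surgery. Hook Plates are followed over an implanted period of varying length plus 12 months after removal. An AE proportion with no stated window is harder to interpret across those two schedules than one tied to a period. As written, the windowed figures also depend on whether an event is attributed to the device or to the procedure, a distinction that does not affect the outcome as defined.

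**Working it through.** **Step 1. Compare the event sets.**

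| Place in the protocol article | Events counted | Onset window stated |
|---|---|---|
| 2.3.7.1, safety outcome | device-related (ADE) or procedure-related AEs | none |
| 2.4.2, general AE reporting | AEs, no relatedness filter stated | none |
| 2.4.2, Clavicle Plates | ADEs | surgery to upper limit of the 24-month visit |
| 2.4.2, Hook Plates, whole period | ADEs | surgery to 12 months after removal |
| 2.4.2, Hook Plates, two sub-periods | ADEs | surgery to removal; 12 months after removal |

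No row combines the event set of 2.3.7.1 with a stated onset window.

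**Step 2. Reproduce the group size.** Section 2.4.1 gives 30 patients per group to be described and 20% dropout. Then 30 / (1 − 0.20) = 37.5, rounded up to 38 per group, and 2 × 38 = 76. This agrees with the stated enrolment and is not in question. It supplies the denominator, taking the full analysis population to be the 38 enrolled per group.

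**Step 3. Effect of one patient.** Let a be the number of patients with at least one ADE in the window, and b the number whose only qualifying events are attributed to the procedure and not to the device.

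- Windowed risk as planned: a / 38
- Windowed risk for the outcome as defined: (a + b) / 38
- Difference: b / 38, which is 1/38 = 2.6 percentage points for each such patient, whatever a is

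**Step 4. Illustration.** The documents state no AE rate, so a and b are assumptions chosen only to show the scale. Take a = 4 and let b run from 0 to 4. The intervals are 95% Clopper-Pearson, the method named in 2.4.2.

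| b | Risk | 95% CI |
|---|---|---|
| 0 (ADEs only) | 4/38 = 10.5% | 2.9 to 24.8 |
| 1 | 5/38 = 13.2% | 4.4 to 28.1 |
| 2 | 6/38 = 15.8% | 6.0 to 31.3 |
| 4 | 8/38 = 21.1% | 9.6 to 37.3 |

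Across this range the two definitions differ by 0 to 10.5 points (4/38). The intervals overlap widely, as expected at this sample size. The difference is one of definition and not of sampling error, so more patients would not remove it.

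**The case against.** The strongest reply is that nothing is lost from safety reporting. The opening AE lines of 2.4.2 carry no device filter, give exact intervals and use the full analysis population. Tables 2 and 3 schedule AE assessment to 24 months for Clavicle Plates and to 12 months after removal for Hook Plates, so the general AE rates are bounded in practice by scheduled follow-up. This stands. A reader might infer that procedure-related events disappear from the safety results or from a primary safety figure. The text supports neither, because the general rates keep these events and no safety figure is ranked as primary.

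A second reply is that attribution is not either/or. One event can be related to both device and procedure, and possibly related is a low threshold, so an infection or loss of fixation with any plausible device link remains an ADE. This also stands. Only patients with purely procedural events count towards b, which may be few. Nor do the documents say who judges relatedness, so an argument that implanting surgeons would steer events towards the procedure has no basis in them. Several planned outputs do not depend on that judgement: fracture union, all implant removals with reasons, complaints by NRS threshold, and the central image reading.

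Third, the abstract might be read as a competing definition. It is a condensed list that opens with "Outcome measures include adverse events related/potentially related to the investigational device", and need not be exhaustive.

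Finally, the SAP and the Supplementary Material are not shown, and extra AE tables are ordinary SAP content. That answers a complaint about missing detail. It does not answer this point, because 2.4.2 already fixes the event set, the periods and the onset rule for the windowed risks, and that event set is narrower than the one in 2.3.7.1. What the reply leaves open is that the SAP may already add the wider set.

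**Conclusion.** The point holds as a minor inconsistency. Safety is defined on device- or procedure-related AEs, while the risks with a stated onset window, including both Hook Plate sub-periods, are defined on ADEs only. The general AE rates cover procedure-related events but have no onset cut-off and no split at plate removal, so they do not give the matching period-specific risk.

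The size is 2.6 percentage points for each patient whose only events are attributed to the procedure, assuming 38 patients in the group's analysis population. The number of such patients cannot be derived from the documents, and it may be small or zero. The counts in the illustration are assumed and predict nothing about this study. The enrolment figure of 76 is unaffected.

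**What to change.** In section 2.4.2, keep the ADE risks as they are and add the same risks for device- or procedure-related AEs as defined in 2.3.7.1. Use the same onset rule, denominator and Clopper-Pearson interval. Report them to 24 months for Clavicle Plates and, for Hook Plates, over the whole period and both sub-periods. One sentence in the protocol or the SAP would do this.

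The cost is a few table rows. Provided procedure-related AEs are collected with onset dates, as the safety definition and the ADE onset rule imply, no new data are needed and the sample size does not change. The wider risk cannot be lower than the ADE risk, so the sponsor may have to show a less favourable figure beside the present one.

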##### Clinical performance

2.3.7.2

Outcome measures related to clinical performance to be recorded are a subset of safety-related parameters including:
▪Incidence of complaints related to plate prominence or discomfort▪Incidence of complaints related to local pain▪Reoperation rate due to AE probably or possibly related to the investigational device▪Fracture union rate▪Rate of stable AC joint healing (if applicable) at one-year post-removal, clinically assessed

##### Bone and joint healing

2.3.7.3

Bone healing and AC joint healing (in case of Clavicle Hook Plates only) will be assessed by the treating surgeon following local SoC. The global clinical assessment of the patient's status according to the surgeon's judgement will be documented as not assessable, no signs of healing, healing in progress (normal but slow), healing in progress (normal) or healed. In patients receiving Clavicle Hook Plates, the AC joint healing status will be assessed only after the plate has been removed. The global assessment from the surgeon on the joint healing will be documented as: not assessable, not healed, partially healed, or healed.

##### Surgeons' evaluation

2.3.7.4

Surgeons will be asked to evaluate their subjective experience with the Clavicle Plate/Clavicle Hook Plate system using the following two 5-point Likert scale questions:
Surgical time (skin-to-skin) required for fracture reduction and fixation (answers ranging from “much less time than with other implants” to “much more time than with other implants”)Surgeons' impression of the device fit (answers ranging from “implant fitted well, no contouring required” to “implant required contouring medially and laterally”).

##### Functional outcomes

2.3.7.5

Functional outcomes used in this study include the Disabilities of the Arm Shoulder and Hand (DASH) short form (QuickDASH), an occupational health and disability questionnaire (officially translated in 54 languages) (21, 22). Scaling ranges from 0 (least disability) to 100 (most disability). The minimal detectable change (MDC) at the 95% confidence level (MDC95) for QuickDASH has a mean of 18 (range: 16–20), though some indicators place the minimal clinically important differences at or below this threshold.

##### Patient-reported outcomes

2.3.7.6

PROs used in this study are the Patient-Reported Outcomes Measurement Information System (PROMIS®) (23), a set of person-centered measures that evaluate and monitor physical, mental, and social health in adults and children. The PROMIS® Physical Function Upper Extremity Short Form 7a v2.0 (2018) consists of seven questions to evaluate activities requiring use of the upper extremity (shoulder, arm and hand).

Additional PROs including local pain, local discomfort and plate prominence will be assessed using an NRS. The local pain NRS (24, 25), scale ranges from 0 (no pain) to 10 (worst imaginable pain), where pain NRS ≥5 (severe pain) will be considered as an AE. The NRS for local discomfort related to the plate ranges from 0 (no discomfort) to 10 (maximum degree of discomfort imaginable). Patients reporting discomfort NRS ≥1 will be asked if the discomfort produced by the plate requires medical or surgical treatment. If such treatment is required, it will be considered an AE. The plate prominence NRS ranges from 0 (no prominence) to 10 (maximum level of prominence). Patients reporting plate prominence NRS ≥1 will be asked if they require medical or surgical treatment to address the prominence. If treatment is required, it will be considered an AE.

##### Implant removal

2.3.7.7

The rate of implants removed during the study together with the reasons and timing of removal will be analyzed. Data collected include date of surgery and reason for removal. If the implant is removed due to an AE or device deficiency, this will be documented on the specific form. In patients with Clavicle Hook Plates, upon plate removal the stability of the shoulder ligaments will be assessed intraoperatively. The AC joint stability will be assessed as stable, partially unstable, or unstable.

##### Device deficiencies

2.3.7.8

All device deficiencies will be reviewed, determined and documented in writing whether they could have led to a serious ADE.

##### Radiographic outcomes

2.3.7.9

Radiological images will be taken per local SoC, and images will be transmitted to the sponsor. The central reader (a medical specialist with the appropriate training [SL]) will receive the images in a blinded way (no personal patient data except gender), and central analysis will be done at the interim analysis and at the end of the study. The following parameters will be assessed at both time points:
Screw density and distributionQuality of reductionAC and CC distanceBone unionOsteolysis (of the acromion)Heterotopic ossification (in any site)

### Statistical analysis

2.4

This is an observational case series aiming to collect data on clinical performance, safety and usability of Clavicle Plates and Clavicle Hook Plates. Therefore, there is no formal statistical hypothesis in this study.

#### Sample size determination

2.4.1

The study objective is to describe long term outcomes (status following healing of the related clavicle injuries) in a minimum of 30 patients with shaft fractures treated with Clavicle Plates and 30 patients with lateral fractures/AC dislocations treated with Clavicle Hook Plates. Assuming a 20% dropout rate at two years, the study will need to enroll 76 patients (38 patients per group).

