#### Recruitment

2.3.3

The recruitment period will be 15 months, during which at least 76 patients are planned to be enrolled. The participating sites will identify all eligible patients according to the defined inclusion and exclusion criteria. Eligibility assessment will be performed by the investigator and/or adequately trained research team member(s). The eligibility assessment includes but is not limited to an inquiry about the interest and willingness of the patient to participate in the study. Eligible patients identified after treatment (e.g., in case of an acute trauma followed by an emergency surgery) can be consented and enrolled at the latest by the time of discharge. Data collection for the study in the case report form (CRF) is not allowed without the documented agreement of the patient.

All consented patients included in the study will be allocated a unique patient number. Each site will keep an identification list linking the patient number to personal information. The identification list is always kept in a safe and locked place. Sites are not allowed to share the identification list with any third party except for the sponsor representative, legal authorities, and EC/IRB who may access the identification list during on-site monitoring/auditing performed on site.

All consented patients should be followed up within the study for a maximum of 2 years, except if their study participation is prematurely terminated.

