#### Data collection

2.3.4

Tables 2, 3 show data to be recorded for Clavicle Plates and Clavicle Hook Plates. Figure 1 presents the planned patient flow.

**Table 2 T2:** Study schedule for patients with clavicle plates (lateral, shaft, and medial).

Assessment parameters	Pre- intra- and postoperative visits*							
	Visit 1	Visit 2	Visit 3	Visit 4	Visit 5	Visit 6	Visit 7^#^	Visit 8^#^
	Screening/preoperative	Intraoperative (Day 0)	2 (±1) weeks	6 (±1) weeks	3 months (±2 weeks)	6 (±1) months	12 (±1) months	24 (±2) months
Patient information/consent^1^	X							
Eligibility^1^	X							
Patient characteristics	X							
Surgical details		X						
Adverse events		X	X	X	X	X	X	X
Device deficiencies		X	X	X	X	X	X	X
Bone healing				X	X	X	X	X
Surgeons’ evaluation		X						
QuickDASH	X^2^		X	X	X	X	X	X
Patient-reported outcomes^3^								
PROMIS Upper Extremity	X^2^		X	X	X	X	X	X
Local pain			X	X	X	X	X	X
Local discomfort			X	X	X	X	X	X
Plate prominence			X	X	X	X	X	X
Implant removal^π^			X	X	X	X	X	X
Images (x-ray/CT scan)^4^	X	X	X	X	X	X	X	X

CT, computed tomography.

* All postoperative follow-up visits with the defined time windows are calculated from the day of surgical treatment (i.e., Day 0).

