##### Follow-up schedule

2.3.4.5

Follow-up visits with defined time windows will be calculated from either the treatment day (Day 0) or the day of implant removal (Day 0′). All patients will be followed up for a maximum of 2 years after Clavicle Plates or Clavicle Hook Plates implantation. To ensure fair comparisons of treatment outcomes, the FU period is defined as follows:
▪For Clavicle Plates (shaft, lateral or medial), Day 0 is defined as the day of surgical treatment with the plate.▪For Clavicle Hook Plates, Day 0 is defined as the day of surgical treatment with the plate. Scheduled FU visits will be calculated from Day 0 until the plate is removed. After the plate is removed, the subsequent FU visits will be calculated from the day of removal (Day 0′)

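### The 38 Clavicle Plate patients do not secure the stated minimum of 30 shaft fractures, because the group is defined by device and also takes lateral and medial cases

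*Protocol article*

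**What the plan says.** Section 2.4.1 (Sample size determination) sets two targets for long-term description: "a minimum of 30 patients with shaft fractures treated with Clavicle Plates", and "30 patients with lateral fractures/AC dislocations treated with Clavicle Hook Plates". It then gives the one allowance made and the result: "Assuming a 20% dropout rate at two years, the study will need to enroll 76 patients (38 patients per group". Section 2.3.3 (Recruitment) words the total as a floor, "during which at least 76 patients are planned to be enrolled", while the abstract calls it approximate.

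Elsewhere the Clavicle Plate group is described by device:

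- The inclusion criteria (2.3.1) accept Clavicle Plates for fixing clavicle fragments and name no location. The exclusion criteria (2.3.2) remove stable fractures and sternoclavicular fixation, but not lateral or medial fractures.
- Table 2 in section 2.3.4 is titled "Study schedule for patients with clavicle plates (lateral, shaft, and medial".
- Section 2.3.4.5 (Follow-up schedule) says "For Clavicle Plates (shaft, lateral or medial), Day 0 is defined as the day of surgical treatment with the plate".
- Section 2.4.2 reports the 24-month risk of adverse device effects for all patients treated with Clavicle Plates, and starts the interim analysis on 30 patients in each group. Neither refers to shaft fractures.

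**The concern.** The population counted in the size justification (shaft fractures) is narrower than the population that can fill the group (any Clavicle Plate patient). The only inflation is for dropout, so every lateral or medial patient among the 38 takes a place that the calculation gives to a shaft fracture.

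The study has no formal hypothesis, so this count is its only justification of size. At stake is whether the final report can say that it met its target. It may describe fewer than 30 shaft fractures at two years, or present a mixed-location group as if it were the promised shaft series. The Hook Plate target does not have this mismatch: its stated injuries are the ones that the inclusion criteria give for that device.

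**Working it through.** **Inputs.** Target of 30 shaft completers, dropout of 20%, 38 per group and 76 in total, all from section 2.4.1. The shaft share s of the Clavicle Plate group is not given, so it is an assumption and is shown as a range.

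**1. The plan's own figure.** Enrolment per group = 30 / (1 − 0.20) = 37.5, rounded up to 38; 2 × 38 = 76. Both figures reproduce exactly, as a dropout-only inflation.

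**2. Slack.** Expected completers = 38 × 0.80 = 30.4, which is 0.4 above the minimum. For 30 expected shaft completers, the shaft share must be at least 30 / 30.4 = 98.7%. In a group of 38 this means that every patient is a shaft case, since 37/38 = 97.4%.

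**3. Effect of k non-shaft patients among the 38.** Expected shaft completers = (38 − k) × 0.80.

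| k | Expected shaft completers |
|---|---|
| 0 | 30.4 |
| 1 | 29.6 |
| 2 | 28.8 |
| 4 | 27.2 |

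With k = 9, only 29 shaft patients are enrolled, so the minimum is out of reach even without dropout.

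**4. Effect of an assumed shaft share.** Expected shaft completers = 38 × 0.80 × s. The chance of at least 30 is the upper tail of a binomial with n = 38 and probability 0.80 × s. Enrolment needed = 30 / (0.80 × s), rounded up.

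| Assumed s | Expected shaft completers | Chance of at least 30 | Clavicle Plate enrolment needed | Total with 38 Hook Plate patients |
|---|---|---|---|---|
| 100% | 30.4 | 66% | 38 | 76 |
| 90% | 27.4 | 22% | 42 | 80 |
| 80% | 24.3 | 4% | 47 | 85 |
| 70% | 21.3 | 0.3% | 54 | 92 |

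The chances assume that patients are independent and that dropout does not depend on location. The 66% in the first row is what inflating by expected dropout gives in the best case; it is a reference value and not a separate criticism.

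**The case against.** **The arithmetic is right.** It is, and a reader might infer a calculation error where there is none. The fault lies in what the 38 counts.

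**The 38 may already mean shaft fractures.** Section 2.4.1 names shaft patients and then speaks of 38 per group, and section 2.3.3 makes 76 a floor, so lateral and medial cases could come on top. This reading is possible, but the article does not state it. It sits badly with an approximate 76 in the abstract and with a total of exactly 2 × 38, which leaves no room for additional cases.

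**The words shaft, lateral and medial may name plate types.** They follow the device name in Table 2 and section 2.3.4.5, so those two places are weaker evidence of fracture mix. The inclusion criteria still do not restrict Clavicle Plates to shaft fractures.

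**A quota may stand in the full protocol.** The article condenses that document, so the absence of a quota here does not prove that none exists. The mismatch between the target and the group definition is nevertheless in the printed text. A SAP prepared before the final analysis can define populations but cannot change who was enrolled.

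**The consequence is modest.** This largely stands. No power depends on the 30, and adverse event rates use the full analysis population irrespective of dropout. With zero events, the upper 95% Clopper-Pearson limit is 1 − 0.025^(1/30) = 11.6% for 30 patients and 1 − 0.025^(1/27) = 12.8% for 27.

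**A stronger reading to avoid.** A reader might infer that the slack must also absorb ineligible patients, since section 2.1 reports 43 enrolled and 42 eligible. The documents do not support adding this. Section 2.3.6 lists screening failure after enrolment among the reasons for termination recorded on the dropout form, so such patients may already lie within the 20%. The one case is also not split by device.

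**Conclusion.** The point holds as an inconsistency between the counted and the enrolled population. As printed, 38 Clavicle Plate patients do not secure 30 shaft fractures at two years: the slack is 0.4 patient, and one lateral or medial case among the 38 brings the expected number to 29.6. That result needs only the plan's own 20% dropout and the reading that the 38 are Clavicle Plate patients of any location.

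The size of any larger shortfall rests on a shaft share that the article does not give; 27.4, 24.3 and 21.3 belong to assumed shares of 90%, 80% and 70%. A reader might infer that the study is likely to miss its minimum. Without a shaft share or a known enrolment rule, the documents do not support that. They show that the minimum is not protected, and the correction is worth making because this is the only size justification and the remedy is cheap.

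**What to change.** In section 2.4.1, restate the target as 30 patients treated with Clavicle Plates (shaft, lateral or medial) with data at two years. Beside it, give the expected number of shaft fractures for a stated shaft share. Report Clavicle Plate results by fracture location, using the AO/OTA and Robinson classes already recorded under Injury details (2.3.4.2), so that a mixed group is not presented as meeting a shaft target. This needs no new data and leaves the total at 76. The cost is that the claimed number of shaft fractures becomes smaller.

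If the sponsor does intend 38 shaft fractures, the article should say that only shaft fractures count towards the 38, that other locations are enrolled in addition, and that the total then exceeds 76 (for example 80 at an assumed 90% shaft share and 85 at 80%). Section 2.1 reports 43 patients enrolled so far, so the count can still be steered during recruitment.
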